## Abstract

**Background::**

Heart failure (HF) is one of the primary causes of the increasing public health costs, incidence rate and mortality of heart disease. As treatment options for the HF have evolved, people have a better understanding of overall burden of HF, resulting a more centralized method for the treatment of these patients with chronic diseases. At present, with the rapid progress of medical technology, the nursing mode must be updated accordingly. The objective of this trial is to investigate the effects of the program of nursing care and follow-up on life quality, self-care, and the rehospitalization of patients with HF.

**Method::**

This is a randomized controlled study to be carried out from November 2020 to March 2021 and was granted through the Ethics Committee of Changshan County People's Hospital (CCPH002376). The patients meet the following criteria will be included: the age of the patients is 18 years and above, and the functional classification is NYHA II or NYHA III. The patients with the following criteria will be excluded: patients who have received the by-pass surgery in the last 6 months; cancer patients are given radiotherapy or chemotherapy; patients with severe renal failure requiring dialysis; patients with chronic obstructive pulmonary disease who need ventilation; and patients with hearing or visual impairment. In our experiment, patient information scale, the life quality scale (The Left Ventricular Dysfunction Scale) and Self-Care of HF Index are utilized for the assessment. All the analyses are implemented with SPSS for Windows Version 20.0.

**Results::**

Impact of experimental programs on outcomes will be illustrated in the Table.

**Conclusion::**

We hypothesize that the nursing care conducted for the HF patients may improve the life quality and self-care.

**Trial registration number::**

researchregistry 6129.

## Introduction

1

Heart failure (HF) is one of the primary causes of the increasing public health costs, incidence rate and mortality of heart disease.^[1,2]^ In the United States alone, more than 4 million people suffer from the congestive HF each year, and more than 550,000 cases are reported each year.^[3]^ About 1 to 3 percent of adults are diagnosed with the heart disease, and in their lifetime, 1/5 of them develop HF, and incidence rate increases with the age.^[4]^ In the natural process of HF, people will undergo the acute attacks and need hospitalization and emergency medical treatment. It is predicted that in the next decade, the number of people hospitalized for the HF will increase significantly, which will put more and more pressure on the system of health care.^[5,6]^ As treatment options for the HF have evolved, people have a better understanding of overall burden of HF, resulting a more centralized method for the treatment of these patients with chronic diseases.

In these methods, care is an important part, which is designed to help people who have experience with illness make changes in their behavior conducive to good health. At present, nursing practice is seeking to conduct the interventions based on evidence in the clinical settings, with particular emphasis on outcome assessment.^[7,8]^ The HF patients encounter great difficulties in their self-care. Lee et al^[9]^ have reported that if the patients with HF could regularly monitor their symptoms, the management of self-care could be refined and the rehospitalization rates of these patients could be decreased. At present, with the rapid progress of medical technology, the nursing mode must be updated accordingly. The objective of this trial is to investigate the effects of the program of nursing care and follow-up on life quality, self-care, and the rehospitalization of patients with HF.

## Methods

2

This is a randomized controlled study to be carried out from November 2020 to March 2021. This trial is implemented in accordance with the SPIRIT Checklist for the randomized researches and was granted through the Ethics Committee of Changshan County People's Hospital (CCPH002376), and this trial was registered with research registry (researchregistry6129).

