### Randomization

2.1

This study includes 90 HF patients. A random number is assigned to all the patients through utilizing via using a random number table, and the allocation result is hidden in a random envelope. Patients are divided randomly into the study group and control group, each group is assigned 45 people. The patients with the following criteria will be excluded: patients who have received the by-pass surgery in the last 6 months; cancer patients are given radiotherapy or chemotherapy; patients with severe renal failure requiring dialysis; patients with chronic obstructive pulmonary disease who need ventilation; and patients with hearing or visual impairment.

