### Nursing Interventions

2.2

In control group, patients are given the standard nursing in the HF outpatient clinic. The doctor carries on the physical examination to the patient, then prescribes the medicine to patient, ultimately, arranges the appointments of outpatient follow-up. The questions of patients are answered by nurse-researcher.

In intervention group, the patients are given the education manual on the basis of the theory of self-care for HF. Moreover, they are also offered a set of magnetic induction instructions that they should pay attention to in their daily life. The patients are asked to attach magnets to their refrigerators so they could easily follow up on their daily visits and be alerted. After baseline data are taken from patients in intervention group, the patients are followed up by nurse researchers on the phone every 2 weeks for the period of 6 months. Nurse researchers carry out the physical examination for the patients, and provide the personal education and then tell the patients how to carry out some relevant daily monitoring. On the basis of the personal daily lifestyle, the prescribed medications can be adjusted by educational intervention. At the clinic, the patients need to bring the training materials with them. Their symptoms, for instance, the blood pressure, edema, taking additional diuretics as well as the levels of their exercise at home are examined. Through the provision of education manuals and personal education, we strive to improve the knowledge and awareness of the patients. By using the educational manuals designed via nurse researchers, magnet supports the telephone follow-up and educational materials to ensure monitoring of individual symptoms, adherence to treatment, and the identification of symptoms, in an attempt to develop the maintenance of self-care. Outpatient consultation and follow-up also contributes to the management of self-care.

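### The stated study period (November 2020 to March 2021, about 5 months) is shorter than the 6-month programme and the month-6 outcome rows it has to contain

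*Protocol article*

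**What the plan says.** The calendar period appears twice in the protocol article. Section 2 (Methods) says: "This is a randomized controlled study to be carried out from November 2020 to March 2021". The Method paragraph of the Abstract repeats it: "This is a randomized controlled study to be carried out from November 2020 to March 2021 and was granted through the Ethics Committee". Neither place calls the period recruitment or enrolment, and no later date for last follow-up appears anywhere in the article.

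Section 2.2 (Nursing Interventions) sets the length of the programme. Once baseline data are taken in the intervention group, "the patients are followed up by nurse researchers on the phone every 2 weeks for the period of 6 months".

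Table 1 in the Results section lays out the outcomes for two groups of 45. Self-care maintenance has three intervals, the last covering months 5 to 6. The Left Ventricular Dysfunction Scale has rows at months 2, 4 and 6. Rehospitalization, hospitalization costs and complications have one row each with no time window. Section 2.1 (Randomization) gives the total: "This study includes 90 HF patients".

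**The concern.** Two statements in the same article cannot both be carried out as written. A study that starts and finishes within five calendar months cannot contain a six-month programme and a month-6 assessment, and the recruitment of 90 patients has to fit into the same five months. This is a conflict between stated figures, so the fact that an article condenses a fuller protocol does not explain it.

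The practical risk is that someone treats March 2021 as the closing date and analyses then. The last quality-of-life row would be empty, and the last self-care interval would be incomplete for everyone. Months 2 and 4 would be available only for earlier entrants. Rehospitalization, total cost and complications would be counted over follow-up that depends on each patient's entry date. The t-tests and chi-square tests in section 2.4 take no account of follow-up time. Randomisation should spread entry dates evenly over the two groups on average, so the main harm is lost information and rates with no defined time base, and less a bias towards one group.

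**Working it through.** **Inputs**

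- Study period: November 2020 to March 2021 (Abstract; section 2). The widest reading is used: first patient on 1 November 2020, last day 31 March 2021.
- Programme: 6 months from baseline with a call every 2 weeks, intervention group (section 2.2).
- Assessments: months 2, 4 and 6 for the scale, and intervals ending at months 2, 4 and 6 for self-care, both groups (Table 1).
- Sample: 90 patients, 45 per group (section 2.1; Table 1).

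**Step 1. Length of the stated period.** Days by month: 30 + 31 + 31 + 28 + 31 = 151 inclusive, so 150 days elapse between the first and last day. At 30.4375 days per month, 151/30.4375 = 4.96 months.

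**Step 2. Time needed for month 6.** From 1 November 2020, month 6 falls on 1 May 2021, which is 181 days. Shortfall for the earliest possible patient: 181 − 150 = 31 days. Every later entrant falls further short. If follow-up ends on 31 March 2021, 0 of 90 patients reach the month-6 scale assessment.

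**Step 3. The last self-care interval.** A patient entered on 1 November 2020 completes month 4 on 1 March 2021 and is in the fifth month during March. The interval for months 5 to 6 can therefore be started by early entrants, but nobody can complete it.

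**Step 4. Earlier assessments.** The latest entry dates that still reach each assessment by 31 March 2021 are:

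| Assessment | Latest entry | Date reached |
|---|---|---|
| Month 2 | about 31 January 2021 | 31 March 2021 |
| Month 4 | about 30 November 2020 | 30 March 2021 |
| Month 6 | none | 1 May 2021 at the earliest |

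**Step 5. Calls, intervention group only.** Within the period: 150/14 = 10.7, so at most 10. Over the whole programme: 26 weeks / 2 = 13. Counting in days gives 181/14 = 12.9, so 12 complete intervals. The article states no number of calls; about 13 is derived from its schedule.

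**Step 6. Spread of follow-up under a March stop.** Entry on 1 November gives 150 days. Entry on 30 November gives 31 + 31 + 28 + 31 = 121 days. Entry on 31 January gives 28 + 31 = 59 days.

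**Step 7. The alternative reading.** If the period is recruitment only, a patient entered on 31 March 2021 reaches month 6 on about 30 September 2021. All 90 could then supply month-6 data, and the study would end about six months after the date the article gives.

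**The case against.** The strongest reply is that the dates may be meant as the recruitment window. The article gives no data cut-off, no last-visit date and no instruction to stop follow-up in March 2021, whereas the per-patient schedule is explicit. A site that follows section 2.2 and Table 1 would go on to month 6 whatever the calendar sentence says. This stands as a possible intention, and it makes the empty month-6 row conditional. It does not remove the conflict: the sentence is about the whole study and never mentions enrolment, and on the recruitment reading the stated end of the study is wrong by about six months.

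Three stronger claims are tempting, and the article does not support them:

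- **That the trial cannot answer its own question.** The objective in the Introduction names quality of life, self-care and rehospitalization without a time point, and nothing makes month 6 primary. Months 2 and 4 are also in Table 1.
- **That both final rows would be wholly empty.** Only the month-6 scale row is. The last self-care interval could be partly observed.
- **That unequal follow-up is planned.** It would follow only from a stop in March 2021. Table 1 sets no window for rehospitalization, cost and complications, and the full protocol may set one.

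Two limits on the figures also stand. The fortnightly calls are described for the intervention group only, so the month-6 requirement for both groups rests on Table 1. The ethics and registry records are not at hand and may already carry separate dates.

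**Conclusion.** The point holds as an error in the stated dates. On the widest reading the period is 150 elapsed days (about 5 months) against the 181 needed, so it is at least 31 days too short for every patient. Nothing in the article reconciles the two.

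The consequences rest on one assumption, that March 2021 is the end of follow-up. Given that, no patient reaches the month-6 scale assessment or completes the last self-care interval, month 4 is limited to entry by about 30 November 2020, at most 10 of about 13 calls fit in the intervention group, and the event and cost outcomes cover unequal follow-up. If the dates are recruitment only, none of this follows, and what remains is a wrong study end date. The text needs correcting on either reading, before any final analysis is scheduled.

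**What to change.** Restate the dates in the Abstract and section 2, giving first enrolment, last enrolment and last follow-up separately. If November 2020 to March 2021 is the recruitment window, say so and set last follow-up at last enrolment plus 6 months, about 30 September 2021.

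State that the final analysis is run only once every randomised patient has passed month 6, died or withdrawn. State also that rehospitalization, cost and complications are counted over the same window, 0 to 6 months from baseline, for each patient in both groups. That common window is a proposal of this review; the article sets none.

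The cost is a later read-out and a date amendment wherever the ethics, registry or other records carry the same dates. No extra patients, visits or procedures are needed.

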### Randomization

2.1

This study includes 90 HF patients. A random number is assigned to all the patients through utilizing via using a random number table, and the allocation result is hidden in a random envelope. Patients are divided randomly into the study group and control group, each group is assigned 45 people. The patients with the following criteria will be excluded: patients who have received the by-pass surgery in the last 6 months; cancer patients are given radiotherapy or chemotherapy; patients with severe renal failure requiring dialysis; patients with chronic obstructive pulmonary disease who need ventilation; and patients with hearing or visual impairment.

### Nursing Interventions

2.2

In control group, patients are given the standard nursing in the HF outpatient clinic. The doctor carries on the physical examination to the patient, then prescribes the medicine to patient, ultimately, arranges the appointments of outpatient follow-up. The questions of patients are answered by nurse-researcher.

In intervention group, the patients are given the education manual on the basis of the theory of self-care for HF. Moreover, they are also offered a set of magnetic induction instructions that they should pay attention to in their daily life. The patients are asked to attach magnets to their refrigerators so they could easily follow up on their daily visits and be alerted. After baseline data are taken from patients in intervention group, the patients are followed up by nurse researchers on the phone every 2 weeks for the period of 6 months. Nurse researchers carry out the physical examination for the patients, and provide the personal education and then tell the patients how to carry out some relevant daily monitoring. On the basis of the personal daily lifestyle, the prescribed medications can be adjusted by educational intervention. At the clinic, the patients need to bring the training materials with them. Their symptoms, for instance, the blood pressure, edema, taking additional diuretics as well as the levels of their exercise at home are examined. Through the provision of education manuals and personal education, we strive to improve the knowledge and awareness of the patients. By using the educational manuals designed via nurse researchers, magnet supports the telephone follow-up and educational materials to ensure monitoring of individual symptoms, adherence to treatment, and the identification of symptoms, in an attempt to develop the maintenance of self-care. Outpatient consultation and follow-up also contributes to the management of self-care.

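### Control patients' questions go to the nurse-researcher, the role that wrote and delivers the programme, which risks passing programme content to controls and diluting the self-care difference

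*Protocol article*

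**What the plan says.** All the relevant text on care is in section 2.2, Nursing Interventions, of the protocol article.

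- Control arm: "In control group, patients are given the standard nursing in the HF outpatient clinic". A doctor examines the patient, prescribes and arranges outpatient follow-up. The paragraph ends: "The questions of patients are answered by nurse-researcher".
- Intervention arm, materials: the manuals come from the same role ("By using the educational manuals designed via nurse researchers"), and patients also receive magnets carrying daily-life instructions.
- Intervention arm, delivery: "the patients are followed up by nurse researchers on the phone every 2 weeks for the period of 6 months". Nurse researchers also examine the patients and "provide the personal education and then tell the patients how to carry out some relevant daily monitoring".

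Section 2.1 randomises 90 individual patients, 45 to each group. Section 2.4 compares groups with independent-samples t-tests and chi-square tests at P < .05. In Table 1, self-care maintenance is the first outcome, reported over three two-month periods.

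**The concern.** The programme consists largely of what a nurse-researcher tells a patient about symptoms, daily monitoring and adherence. A control patient who asks about any of these would be answered by someone in the role that wrote and teaches that material. Nothing in section 2.2 confines the answer to what the clinic would ordinarily say.

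The comparison could then drift from programme versus usual care toward programme versus some programme content on request. Self-care is the outcome that the education targets directly, so it is the most exposed. Contamination of this kind shrinks the difference between groups. A programme that works could therefore look weaker than it is, and with 45 per group it could miss significance. Once controls have received the content, the analysis has no means of removing the dilution.

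**Working it through.** **Step 1: the two arms side by side (section 2.2).**

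| Task | Control | Intervention |
|---|---|---|
| Physical examination | Doctor | Nurse researchers |
| Manual | None described | Designed by nurse researchers |
| Personal education, monitoring advice | None described | Nurse researchers |
| Scheduled telephone calls | None described | Nurse researchers, two-weekly for 6 months |
| Answering patients' questions | Nurse-researcher | Not listed as a separate task |
| Stated limit on what may be said | None | Not applicable |

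The nurse-researcher role appears in both columns. In the control column it appears exactly where self-care advice could be given.

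**Step 2: is there a planned figure to reproduce?** No. The article gives 45 per group without an effect size, SD, power or dropout rate, so its sample size cannot be re-derived.

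**Step 3: how much could dilution matter at this sample size?**

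Inputs from the article: n = 45 per group (section 2.1); t-test and 5% level (section 2.4).

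Assumptions, none of them from the article: a two-sided test; a true effect d = 0.60 SD, chosen because it gives about 80% power at this n; and a fraction c = 10%, 20% or 30% of the programme's effect reaching controls.

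Formulas:
- Diluted effect: d' = 0.60 × (1 − c).
- Noncentrality: λ = d' × √(45/2) = d' × 4.743.
- Degrees of freedom: 45 + 45 − 2 = 88; two-sided critical value 1.987.
- Power: the probability that a noncentral t with 88 df and noncentrality λ falls outside ±1.987.

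| c | d' (SD) | λ | Power |
|---|---|---|---|
| 0% | 0.60 | 2.846 | 80.4% |
| 10% | 0.54 | 2.561 | 71.7% |
| 20% | 0.48 | 2.277 | 61.5% |
| 30% | 0.42 | 1.992 | 50.4% |

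**Step 4: cross-check.** The normal approximation, power ≈ Φ(λ − 1.96), gives 81.2%, 72.6%, 62.4% and 51.3%. These are about one percentage point higher, and the pattern is the same.

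The table shows how sensitive a trial of this size would be to modest dilution. It does not estimate how much dilution would occur.

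**The case against.** The strongest reply is that answering questions belongs to the comparator. The sentence stands in the paragraph that defines standard nursing, and answering questions is not listed among the programme's components. Controls get no manual, magnets or scheduled calls, and two-weekly calls for 6 months come to about 13 (26 weeks ÷ 2). On this reading the trial compares a structured, proactive programme with usual care in which questions are answered, and a large contrast remains.

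Much of this stands. It means contamination is possible and not established, and that any dilution may be small. The article does not say that the same individuals serve both arms; it says only that the role is the same. Nor does it say what controls ask or are told. The reply does not explain why the role that wrote and teaches the programme should be the one answering, when a doctor is already part of control care.

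A reader might also infer that unmasked, self-reported scores are inflated because patients complete the questionnaires in front of the nurse who educated them. The article does not support this as a finding. That patients and delivering nurses know the allocation is a fair inference from the visible materials, and the envelope ("the allocation result is hidden in a random envelope") conceals allocation only. But the article does not say how the scales are completed, who collects them or who scores them, and a condensed article may leave that to the full protocol. Rehospitalization, costs and complications in Table 1 are not questionnaire scores in any case.

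**Conclusion.** The point holds as a risk of contamination built into section 2.2. One role designs and delivers the programme and also answers control patients' questions, under individual randomisation and with no stated limit on the answers. The expected direction is toward no difference, chiefly in self-care.

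The size is unknown. The fall in power from about 80% to 72% at 10% dilution, and to 50% at 30%, rests on an assumed 0.60 SD effect, assumed dilution fractions and an assumed two-sided test. A reader might take the 80% as the trial's planned power; it is not, since the article states none. A reader might also conclude that the control arm is contaminated; the text shows only how it could be. The case for acting is that the remedy is cheap and the dilution could not be undone after data collection.

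**What to change.** In section 2.2, replace the last sentence of the control paragraph so that control patients' questions are answered, as in usual care, by the clinic doctor already named there or by regular outpatient nurses who do not deliver the programme.

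If the nurse-researchers are the clinic's only nurses, state instead that their answers to control patients are limited to usual-care content and that each such contact is logged with its topic. The log would at least show how often controls asked about material the programme covers.

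Cost: a wording change. The first option relies on a doctor already involved in control care, or on regular nurses where the clinic has them; the second adds a short contact record. The downside is that control patients may receive slightly less uniform answers.
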